#### Sample size and power analysis

A power analysis using the G*Power software (Faul et al., 2007) will be performed in estimating the required sample size. To detect a medium effect size of 0.50, with alpha set at 0.05, and power of 0.80, a minimum sample size of 128 is required. Based on recommendations from Hall and Bierman (2015) review of high attrition from technology-assisted parenting intervention, this study will allow an attrition of 50%, making the target sample size 200, with 100 participants for each group.

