### Statistical analyses

Multivariate analysis of covariance (MANCOVA) will be employed to compare the mean of the outcome variables at pre-assessment, post-assessment, and 1-month follow-up between the two groups (i.e., DaPI vs. WLC). Pairwise comparisons will be performed to identify specific differences in the outcome variables between the groups. Similarly, intention-to-treat analysis (ITT) will be conducted on the data to allow all participants to be included in the analysis, regardless of whether they withdrew from the study or did not complete the intervention. Missing data will be treated using multiple imputations, which is a relatively flexible, general approach for dealing with missing data. The intervention will be considered effective if the parents in the DaPI group show more improvement over time on one of the outcome variables compared to the control group, at a significance level of 0.05, and at small to medium effect size *d* [0.2–0.5].

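### The success rule requires d to lie between 0.2 and 0.5: read literally it fails effects above 0.5, and read as a minimum it adds nothing to the unadjusted test used for sizing

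*Protocol article*

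**What the plan says.** The last sentence of Statistical analyses defines success. DaPI counts as effective if its parents improve more over time than controls on one of the outcome variables, at a significance level of 0.05, "and at small to medium effect size"; a bracket gives d as 0.2 to 0.5. The word *and* makes the effect size a second condition beside significance. The article does not say whether the bracket is a minimum, a closed interval or an expected range. Nor does it say whether d is raw or covariate-adjusted.

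The section Sample size and power analysis uses a single effect: "To detect a medium effect size of 0.50, with alpha set at 0.05, and power of 0.80", for which "a minimum sample size of 128 is required". It then states that "this study will allow an attrition of 50%, making the target sample size 200", "with 100 participants for each group".

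**The concern.** This sentence is the article's only definition of success, so its exact content matters. An effect-size range with an upper limit is an odd condition for effectiveness, because a better result can fail it. The upper limit also equals the effect the trial is sized for, so about half of all estimates would exceed it if the design assumption were exactly right. The lower limit looks like a relevance threshold, but it may sit below anything the trial could find significant.

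Two things are at stake. The 80% power behind the sample size may not apply to the rule that will be used. And the same data can give opposite verdicts depending on how the bracket is read: an observed d of 0.6 at 100 per arm has p < 0.001, yet lies outside the range.

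**Working it through.** **Inputs.** From Sample size and power analysis: d = 0.50, alpha 0.05, power 0.80, 128 required, 200 recruited (100 per arm), 50% attrition allowed. From Statistical analyses: significance at 0.05 and d from 0.2 to 0.5. Three sizes are carried through: 100 per arm (no loss), 64 per arm (the 128 required) and 50 per arm (200 × 0.5 = 100 completers). The baseline–outcome correlation r is not given, so it is an assumption shown over a range.

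**Step 1: the plan's own figure.** A two-sample t-test with two-sided alpha 0.05, using the noncentral t distribution, needs 64 per arm for d = 0.50 at 80% power. That is 2 × 64 = 128, as stated. A one-sided test gives 102, so two-sided is the basis used below.

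**Step 2: the smallest significant observed d.** With n per arm, t = d × √(n/2) on 2n − 2 degrees of freedom. The threshold is therefore t(0.975) × √(2/n).

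- n = 100: 1.972 × 0.1414 = 0.279
- n = 64: 1.979 × 0.1768 = 0.350
- n = 50: 1.984 × 0.2000 = 0.397

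An observed d of exactly 0.2 gives two-sided p = 0.159, 0.260 and 0.320 at these sizes. About 194 per arm would be needed before it reached p < 0.05.

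**Step 3: the literal interval.** Both conditions hold when t lies between its critical value and 0.5 × √(n/2), which is 3.54, 2.83 or 2.50 at 100, 64 or 50 per arm. The probabilities come from the noncentral t with noncentrality (true d) × √(n/2), for one outcome.

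| True d | Rule | 100/arm | 64/arm | 50/arm |
|---|---|---|---|---|
| 0.5 | significant, d ≥ 0.2 | 94% | 80% | 70% |
| 0.5 | significant, d 0.2 to 0.5 | 44% | 30% | 19% |
| 0.6 | significant, d 0.2 to 0.5 | 23% | 21% | 15% |
| 0.7 | significant, d 0.2 to 0.5 | 8% | 11% | 9% |
| 0.8 | significant, d 0.2 to 0.5 | 2% | 4% | 5% |

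At a true d of 0.5 the loss is about 50 percentage points at every size (94 − 44, 80 − 30, 70 − 19), which is the half of the estimates that fall above 0.5.

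**Step 4: can a floor of 0.2 bind under adjustment?** If the planned MANCOVA includes the baseline value as a covariate, t = d × √(n/2) / √(1 − r²), with d still on the raw standard deviation. At 100 per arm an observed d of 0.2 gives p = 0.104 (r = 0.5), 0.079 (r = 0.6), 0.049 (r = 0.7) and 0.019 (r = 0.8). The floor can bind from r of about 0.70 at 100 per arm, 0.82 at 64 and 0.86 at 50.

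**Step 5: what the trial can detect (unadjusted).**

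| True d | 100/arm | 64/arm | 50/arm |
|---|---|---|---|
| 0.2 | 29% | 20% | 17% |
| 0.3 | 56% | 39% | 32% |
| 0.4 | 80% | 61% | 51% |
| 0.5 | 94% | 80% | 70% |

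The true d detectable with 80% power is about 0.40, 0.50 and 0.57 respectively. A true d of 0.2 would need 788 completers.

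**The case against.** The strongest reply is that the authors probably meant at least a small to medium effect. The two limits are the values that usually carry those labels, and nothing in the article says a larger effect counts as failure, which would defeat the trial's aim. On that reading the rule can be applied, and where the floor does not bind it reduces to the significance test. This is a fair account of the likely intention, and it means that the losses in Step 3 belong to the literal reading only. It does not rescue the wording: the text joins a two-sided range to the significance condition and does not say that the range is a minimum.

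A reader might go further than the document allows in four ways.

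- *An effect of 0.2 can never be significant in this trial.* This holds for the unadjusted comparison. The article plans MANCOVA without naming covariates, and Step 4 shows that strong baseline adjustment could make 0.2 significant.
- *The trial has little chance of detecting anything from 0.2 to 0.4.* This is true near 0.2, but power at 0.4 is 51% to 80%.
- *Sizing for 0.5 while accepting smaller effects is a contradiction.* It is not. Power concerns the true effect and the success rule most naturally concerns the estimate. A trial with 80% power for 0.5 normally declares success at estimates well below 0.5 (0.35 at 64 per arm).
- *A non-significant result will be reported as proof of no effect.* The article says only when the intervention will be called effective, not how a null result will be read.

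**Conclusion.** The point stands: the effect-size clause should not be part of the success rule as written. Read as an interval, it cuts the chance of success on one outcome at the design effect to about 44%, 30% or 19% (100, 64 or 50 per arm), and that chance falls further as the true effect grows beyond 0.5. Read as a minimum, it does no work in the comparison on which the size is based.

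These figures assume a two-sided, unadjusted t-test, equal arms, one outcome at one time point, and completer counts standing in for the information left after multiple imputation. Baseline adjustment would lower the significance threshold, but an upper limit of 0.5 would still exclude larger effects. How much the clause matters in practice depends on which reading is applied, and the article leaves that open.

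**What to change.** In Statistical analyses, delete the bracketed range and its lead-in from the success sentence. Base success on the between-arm significance test, and report the standardised difference with its 95% confidence interval. If a relevance threshold is wanted, state it as a one-sided minimum on a defined estimate (outcome, time point, raw or adjusted, and which standard deviation), with no upper limit.

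Add a sentence to Sample size and power analysis: in an unadjusted comparison the trial has 80% power for d of about 0.40 if all 200 are retained, 0.50 with 128 completers and 0.57 with 100 completers. A non-significant result therefore does not rule out smaller effects (power of 17% to 29% at d = 0.2 and 32% to 56% at d = 0.3).

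The cost is one changed sentence and one added sentence, with no extra participants or data. The change should be made before outcome data are compared by arm, so that the reading of the bracket is not chosen after the results are known.

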## Discussion

This protocol paper outlines the background and design of an online digital-assisted parenting intervention (DaPI) that aims to promote the mental health of children in Malaysia by targeting parenting behaviors and parental self-efficacy. The DaPI program was designed to be practical and interactive, yet strongly based on research evidence. This RCT will examine whether, in comparison to the control group, parents who received the DaPI program would show significant changes in parenting behavior and parental self-efficacy. Additionally, the RCT will assess whether, in contrast to parents in the WLC group, parents in the DaPI program would report significant changes in their children’s behavioral problems and emotional maladjustment. Overall, it is expected that participating in the DaPI program will improve parenting behavior and confidence as well as reduce children’s behavioral problems and emotional maladjustment. Better knowledge and skills in parenting will help to improve parents’ interaction with their children in an intellectually stimulating and emotionally reassuring way. Thus, making children more emotionally, cognitively, and socially able to manage challenges.

This RCT is timely considering the widespread use of digital devices across the Malaysian population. Due to the COVID-19 pandemic, digital-assisted parenting intervention would be more attractive for parents who are not keen on traditional face-to-face intervention. Moreover, a universal, online, preventive parenting intervention is deemed to be more favorable for working Malaysian parents who would like to receive additional support on parenting practices but have difficulty attending parenting interventions during their working hours. An online intervention such as DaPI would allow anonymity to parents to participate without fear of mental health stigma or judgment regarding their parenting skills. Furthermore, if found effective, the DaPI program can be widely disseminated as a cost-effective universal preventive parenting program for all Malaysian parents, leading to better mental health, quality of life, and overall development for their children.

Improved parenting behavior and parenting self-efficacy can reduce children’s use of primary care services (McGilloway et al., 2014) which would lead to potential cost savings. This could potentially help healthcare professionals focus more time and resources on clinical or at-risk populations. These benefits may prompt advocates and policymakers to explore the promise of and invest in preventive parenting programs to reduce the negative and costly outcomes of mental illness in children. If investments are made in preventive parenting programs, children would have more opportunities to grow to be healthy, protected, and well-developed, thus becoming productive human resources for the progress and development of a nation.

## Ethics statement

The studies involving human participants were reviewed and approved by Universiti Putra Malaysia’s Ethic Committee for Research Involving Human Subjects (JKEUPM-2021-161). The participants provided their written informed consent to participate in this study.
